## Introduction

1

Neck pain is one of the common musculoskeletal disorders in the general population. Although the prevalence of neck pain varies by studies conducted and the time period, the 1-year prevalence rate is reportedly 25.8%^[1]^ and the prevalence in an adult's lifetime is 50%.^[2]^ Neck pain can develop into considerably severe pain, disability, and cause a financial burden.^[3]^ Years lived with disability from neck pain per 100,000 population was reportedly 352 from 1990 to 2017,^[4]^ and the neck pain was the fourth main cause of years lived with disability according to the 2016 Global Burden of Disease.^[5]^

Among the different types of neck pains, acute neck pain is considered a self-limiting disorder and adults can experience pain during typical activities (e.g., lifting, twisting, and stretching). Acute neck pain is caused by loads applied internally to the tissues or external loads such as a fall and direct impact to the head or neck. However, little is known about the prevalence and treatment of acute neck pain, especially those not caused by whiplash. Vernon et al^[6]^ reported that the point prevalence of acute neck pain to be around 10%. There is currently no consensus for the definition of acute neck pain but is often defined as pain that does not last for more than 4 weeks.^[7,8]^ There is no standardized guideline for the treatment of acute neck pain but in a study of patients that visited general practitioners for acute neck pain in the Netherlands, 42% of patients were prescribed non-steroidal anti-inflammatory drugs and muscle relaxation.^[9]^ In addition, other studies have reported on the effectiveness of laser therapy^[10]^ and cervical spine thrust manipulation^[11]^ on acute neck pain.

The motion-style acupuncture technique (MSAT), which combines traditional acupuncture and movement therapy, is a treatment that induces passive and active movements of the patient with the needles inserted, after a traditional acupuncture treatment. All movements are made under the observation and guidance of a physician. MSAT has been increasingly used to relieve musculoskeletal pain in Korean clinical practice and recently has gained attraction in China as a method to enhance the effect of traditional acupuncture treatment.^[12–14]^ However, the supporting evidence and data for the effectiveness and safety of MSAT are insufficient as only a few related studies have been conducted.

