#### Primary outcome: visual analogue scale on movement (VAS on movement)

2.4.1

The primary outcome of this study will be the difference between the baseline (Week 1) and the primary endpoint, week 3 (visit 8) for the neck pain felt during movement. The VAS is an assessment tool on which the patient indicates the level of pain along a continuous line of 100 mm in length, with one end indicating no pain and the other indicating the worst pain possible.^[16,17]^

The VAS of neck pain felt on movement will be measured 7 times in total; at the screening, baseline, the last visit of each week during the intervention period (visits 4 and 7), week 3 (visit 8), and week 8 (visit 9).

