### Statistical analysis

2.11

This study will be a randomized controlled study that analyzes the pain intensity scale, functional scale, quality of life, and costs data results of patients who meet the selection criteria.

The primary analyses will be the intention-to-treat analysis, which evaluates those who have received treatment at least once, and the per-protocol analysis, which evaluates only those who have successfully completed the clinical study, excluding those who have been dropped out; the 2 analyses will be performed concurrently.

For processing the missing values, multiple imputations using the Markov Chain Monte Carlo method will be used as the primary method, and 20 imputed datasets will be generated. In addition, the last observation carried forward method will be used for the sensitivity analysis.

The sociodemographic characteristics and treatment expectancy of the subjects will be evaluated for each of the groups. Continuous variables will be represented as mean (standard deviation) or median (quartiles), and categorical variables will be represented as a frequency (%).

The effectiveness endpoint of this clinical trial will be the difference in the amount of change between baseline and each time point by the group for the continuous outcomes (NRS, VAS, NDI, NPQ, EQ-5D-5L, and SF-12). Analysis of Covariance will be performed using the baseline values of each variable as covariates and the group as a fixed factor.

For the sensitivity analysis, datasets without the imputed values will be used to analyze the degree of change from the baseline. The mixed-effects repeated measures analysis will be performed for the primary and secondary outcomes at all time points. The time variable will be included as a categorical variable and the interaction terms of group and time will be included at each time point to evaluate the difference in the effectiveness of MSAT.

To compare the total amount of difference between 2 groups for each outcome within the treatment period (2 weeks) and the entire study period (8 weeks), the areas under the curve (AUC) within each period after randomization will be calculated. The difference in AUC between the 2 groups will be compared using the independent student *t* test.

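### The one missing-data check that leaves missing-at-random is last observation carried forward, which says little about robustness to informative dropout in a self-limiting condition

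*Protocol article*

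**What the plan says.** The Statistical analysis section (2.11) sets the primary approach: "multiple imputations using the Markov Chain Monte Carlo method will be used as the primary method, and 20 imputed datasets will be generated". It then names LOCF as a check: "In addition, the last observation carried forward method will be used for the sensitivity analysis". Two further analyses follow: "For the sensitivity analysis, datasets without the imputed values will be used to analyze the degree of change from the baseline", and "The mixed-effects repeated measures analysis will be performed for the primary and secondary outcomes at all time points". A per-protocol analysis is run alongside the intention-to-treat analysis. It "evaluates only those who have successfully completed the clinical study, excluding those who have been dropped out".

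The primary outcome (2.4.1) is "the difference between the baseline (Week 1) and the primary endpoint, week 3 (visit 8) for the neck pain felt during movement", on a 100 mm line. Before week 3 the scale is recorded at screening, at baseline, and at visits 4 and 7. The sample size section (2.6) allows for 20% dropout and plans on an effect size of 0.55. The blinding section (2.9) says that physicians and patients cannot be blinded. On the natural course, the Introduction says that "acute neck pain is considered a self-limiting disorder".

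**The concern.** A missing-data sensitivity analysis should show whether the conclusion survives if the primary assumption is wrong. Here that assumption is missing at random, so the useful check is one that departs from it in a controlled and interpretable way. LOCF departs from it, but in a way that nobody would choose for this condition. It assumes that a patient who leaves would have scored the same at week 3 as at the last recorded visit. The protocol describes a disorder that resolves on its own, enrols patients on a score of 5 or higher (which makes a later fall likely), and plans a time-to-event analysis of the score falling below half of baseline.

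Informative dropout is credible in this design. Patients know their arm, they mark the primary scale themselves, and other neck-pain treatment apart from acetaminophen is prohibited until week 3. A patient who is disappointed or still in pain has a reason to leave. At stake is how far a reader can trust the week-3 conclusion if those patients differ from the ones who stay.

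**Working it through.** **Step 1. What each listed analysis assumes.**

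| Analysis in 2.11 | Assumption about missing values |
|---|---|
| Multiple imputation by MCMC, 20 datasets (primary) | Missing at random |
| Mixed-effects repeated measures | Missing at random |
| Data without imputed values | Missing at random given the model covariates, or the stricter missing completely at random |
| Per-protocol set | Completers only; an analysis set, not a model for missing-not-at-random data |
| LOCF | Score frozen at the last visit |

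LOCF is the only row that does not rest on missing at random or something stricter.

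**Step 2. The plan's own figures.** An exact two-sample t calculation with effect size 0.55, two-sided α 0.05 and 80% power gives 53 per arm, 106 in total. The covariance adjustment gives 106 × (1 − 0.24²) = 99.9, so 100. Dropout gives 100 / 0.80 = 125. Equal arms at four sites give 125 / 8 = 15.6, rounded up to 16, and 16 × 8 = 128. All figures reproduce and none is disputed. I take 0.55 and 20% from here; every other input below is assumed.

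**Step 3. How LOCF moves the arm difference.** Let m be the mean improvement to week 3 without dropout, d the dropout proportion, and f the fraction of that improvement already reached at the last recorded visit. The LOCF mean change in an arm is m × [(1 − d) + d × f]. With no true effect, the spurious difference (MSAT minus control) is

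m × [d_C × (1 − f_C) − d_M × (1 − f_M)].

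Its sign depends only on which arm loses more patients or loses them earlier.

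**Step 4. Unequal dropout, no true effect.** Assume 15% in one arm and 25% in the other (9.6 and 16 of 64 patients, averaging the planned 20%), and an SD of 2 points on a 0 to 10 scale (20 mm). Write the missed improvement as m × (1 − f), equal in both arms. The shift is 0.10 × missed improvement.

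| Missed improvement | Shift | In SD | Share of 0.55 |
|---|---|---|---|
| 1 point | 0.1 point | 0.05 | 9% |
| 2 points | 0.2 point | 0.10 | 18% |
| 3 points | 0.3 point | 0.15 | 27% |

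The shift favours MSAT if control loses more, and control if MSAT loses more.

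**Step 5. Equal dropout, same timing.** With 20% in both arms and equal f, the spurious difference is zero. A true 0.55 SD becomes 0.55 × (0.80 + 0.20 × f):

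- f = 0 (baseline carried): 0.55 × 0.80 = 0.44 SD.
- f = 0.5: 0.55 × 0.90 = 0.495 SD.

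**Step 6. Equal dropout, different timing.** With 20% in both arms, m = 1 SD, f = 0 in control and f = 0.5 in MSAT, the spurious difference is 1 × [0.20 × 1 − 0.20 × 0.5] = 0.10 SD in favour of MSAT. Equal dropout rates alone therefore do not make LOCF neutral.

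**The case against.** Five points can be made for the plan.

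- **LOCF is only one sensitivity analysis.** This stands. The primary multiple-imputation estimate is untouched. A reader might infer from the percentages above that the trial's main result is biased by that amount, but they describe bias in the check alone.
- **A delta or tipping-point analysis may sit in an analysis plan that is not shown.** This stands as far as it goes. A reader might infer that the trial has no adequate missing-not-at-random analysis at all, and an article that condenses a fuller protocol cannot support that. The point here is narrower: a method that the article does fix is a poor choice for its purpose.
- **For a patient who leaves because nothing is improving, a frozen score may be close to the truth.** This partly stands. The eligibility criteria also admit recent worsening of older pain. It would therefore be too strong to call the LOCF assumption false for all patients, or to say that agreement with LOCF carries no information. But LOCF applies the same rule to every dropout whatever the reason, and its severity is set by the timing of exit rather than by a stated assumption.
- **Carried values need not be early, high scores.** This stands. A patient who misses only the week-3 visit carries visit 7, and one who leaves in the second week may carry visit 4. The documents give no dropout timing.
- **The dropout split, the missed improvement and the SD are not in the documents.** This stands, which is why the working shows a range, both directions, and equal dropout.

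**Conclusion.** The point holds as a weakness in a named secondary analysis. LOCF is the only listed check outside missing at random or something stricter. Its frozen score is implausible for many patients in a self-limiting condition, and it understates uncertainty by treating carried values as data. Its bias has no fixed direction, so it cannot be relied on as conservative.

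On the assumed inputs, LOCF alone shifts the arm difference by 0.05 to 0.15 SD when dropout differs by 10 percentage points. With equal, similarly timed dropout of 20% it attenuates a true 0.55 SD to 0.44 to 0.495 SD and creates no false effect. Agreement or disagreement with LOCF therefore says little about whether informative dropout could overturn the week-3 conclusion. This is worth correcting before the data are analysed. It does not call the primary analysis, the sample size or the endpoint into question.

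**What to change.** Replace LOCF, or demote it to a supplementary check, with a delta-adjusted analysis on the same 20 MCMC imputations:

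- Worsen only the imputed week-3 VAS on movement, in steps on the 100 mm scale, for example 0, 5, 10 mm and upward. Leave observed values unchanged.
- Do this in the MSAT arm only, and over combinations of shifts in both arms.
- Rerun the planned analysis of covariance at each step, combine across imputations, and report the tipping point at which the primary conclusion changes.

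As a guide to scale, with 20% of an arm imputed, a 10 mm shift in that arm moves the arm difference by 0.20 × 10 = 2 mm, or 0.10 SD at the assumed SD of 20 mm.

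The cost is a short addition to the imputation program in the SAS version already specified. No visit, endpoint or sample size changes. The real work is choosing the delta range and justifying it clinically before the data are seen, because a tipping point is informative only if readers can judge whether that shift is plausible.

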##### Northwick park neck pain questionnaire (NPQ)

2.4.2.4

The NPQ is a questionnaire that consists of 9-question items on daily life activities affected by the neck pain (intensity, sleep, numbness, duration, carrying things, reading/watching TV, working, social activities, and driving). Each question consists of 5 levels with 0 to 4 points, and a higher score indicates more severe consequent patient disabilities.^[21]^ In this study, the Korean version of the NPQ, translated and validated by Lee at al, will be used.^[22]^

NPQ will be measured 3 times in total; at the baseline, week 3 (visit 8), and week 8 (visit 9).

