### Sample size estimation

2.6

To estimate the number of study subjects, the results of the unpublished pilot study was used. Based on the pilot study, the effect size of MSAT for patients with neck pain is 0.55. When estimating the number of samples while using the *t* test as the primary analysis, the result showed that 106 subjects in total (53 per group) will be required. However, since the analysis of covariance is the primary analysis in this study, using the correlation coefficient of the mean difference between the baseline value and primary endpoint calculated through the pilot study, 0.24, the corrected number of samples was determined to be 100. Considering a dropout rate of 20% and recruitment from 4 institutions, a total of 128 subjects (64 subjects per group) were calculated as the number of samples required to conduct the clinical trial.

The calculation was performed based on the assumption level of significance at α=0.05 (2-sided test) and 80% of the power of the test with type 2 error (β) at 0.2. G∗Power 3.1.9.7 was used to estimate the sample size.

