Survival analysis for VAS of neck pain will be performed. At each time point, the patient ratio will be comparatively analyzed for each time point when the neck pain VAS falls below half of the baseline. A Kaplan–Meier survival analysis will be used to estimate the time until less than half of the neck pain recovery occurs after randomization, and the differences between groups will be compared using a log-rank test. Also, the Cox model will be used to estimate the hazard ratio.

All statistical analyses will be performed using the SAS version 9.4 statistical package (SAS Institute, Cary, NC) with the significance level set to *P* < .05. In addition, the analysis will be performed after the end of the study (when all patients follow-ups have been completed) and interim analysis will not be allowed.

In addition, this study aims to investigate the cost-effectiveness between MSAT and acupuncture treatment through an economic evaluation. The primary economic endpoint will be the incremental cost-effectiveness ratios of cost per Quality Adjusted Life Years (QALY) of the MSAT group against the acupuncture treatment group. The analysis period is the entire study period including the intervention period and follow-up period, and if estimation for the subsequent period is required, the costs and effectiveness after the follow-up period will be estimated by extrapolation through a regression model or a secondary analysis with decision modeling analysis.

Medical costs will be calculated based on the number of treatments and the unit cost. For the unit cost, data on health insurance costs, institutional cost data, and patient answers will be used. The quality of life estimation for the QALY calculation, the quality of life derived by EQ-5D-5L will be used as the main endpoint, and EQ-VAS, and SF-6D will be used for the sensitivity analysis. The AUC method will be used for calculation. The units for the costs will be unified in Korean currency (won) as of 2020 and a 5% discount rate will be applied based on the guidelines for the economic evaluation of the Health Insurance Review and Assessment Service and represented in US dollars using the published exchange rate.

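### The AUCs are compared by an unadjusted t test although the same outcomes are analysed by ANCOVA on baseline, so these supporting analyses lose precision and stay exposed to chance baseline imbalance

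*Protocol article*

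**What the plan says.** Section 2.11 sets out two treatments of the same outcomes.

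- Change from baseline at each time point (NRS, VAS, NDI, NPQ, EQ-5D-5L, SF-12): "Analysis of Covariance will be performed using the baseline values of each variable as covariates and the group as a fixed factor".
- Whole-period summaries of each outcome, over the 2-week treatment period and the 8-week study: "the areas under the curve (AUC) within each period after randomization will be calculated". Then: "The difference in AUC between the 2 groups will be compared using the independent student" t test. No covariate is named. The text does not say whether the area is taken over raw scores or over changes, or whether it includes the baseline point.

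VAS on movement is measured "at the screening, baseline, the last visit of each week during the intervention period (visits 4 and 7), week 3 (visit 8), and week 8". NRS and NDI have the same schedule from baseline on. Other instruments are sparser: "NPQ will be measured 3 times in total; at the baseline, week 3 (visit 8), and week 8 (visit 9"), and EQ-5D-5L and SF-12 follow that schedule too.

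The sample size section (2.6) reduces the required number because ANCOVA is the primary analysis, "using the correlation coefficient of the mean difference between the baseline value and primary endpoint calculated through the pilot study, 0.24".

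For QALYs derived from EQ-5D-5L, the economic text says only "The AUC method will be used for calculation", with a bootstrap interval for the cost-effectiveness ratio.

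**The concern.** The protocol uses baseline as a covariate when it compares single time points and drops it when it compares areas built from the same scores. This is a named method, not a detail left to another document.

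The area runs from randomisation, and baseline is the only measurement at that point, so a standard trapezoid includes it. An unadjusted comparison then carries a pre-treatment component that treatment cannot affect. Two things follow. The interval is wider than it need be. And if the arms differ at baseline by chance, part of the AUC contrast is that difference, so the ANCOVA and AUC results for one outcome can diverge for a reason unrelated to treatment.

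**Working it through.** **The plan's own figures first.** For effect size 0.55, two-sided α 0.05 and 80% power, the noncentral t gives 52.87, so 53 per group and 106 in total. The ANCOVA correction is 106 × (1 − 0.24²) = 106 × 0.9424 = 99.9, so 100. Dropout: 100 / 0.8 = 125; 128 divides evenly over 4 sites and 2 arms. The chain reproduces. It also supports reading the loosely worded 0.24 as the baseline-to-follow-up correlation.

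**Inputs for the AUC.** From the protocol: 0.24, the visit schedule, 64 per arm. Assumed: trapezoid over raw scores from baseline, equal SDs (set to 1), correlation ρ between follow-up visits of 0.5 to 0.7, and the visit days shown.

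**Formula.** With trapezoid weights w and correlation matrix S, the correlation of AUC with baseline is r = (w′S)₀ / √(w′Sw). Adjusting for baseline cuts the variance by r².

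*2-week AUC, weeks 0/1/2.* Weights 0.5, 1, 0.5; baseline weight 0.5/2 = 25%.
- Covariance with baseline: 0.5 + 0.24 × 1.5 = 0.86.
- Variance: 1.5 + 0.36 + ρ = 2.36 (ρ = 0.5) or 2.56 (ρ = 0.7).
- r = 0.56 or 0.54; cut 31% or 29%.

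*2-week AUC, days 0/4/11* (plausible because the protocol labels baseline as week 1 and measures at the last visit of each week). Weights 2, 5.5, 3.5; baseline weight 2/11 = 18%.
- Covariance: 2 + 0.24 × 9 = 4.16.
- Variance: 46.5 + 8.64 + 38.5ρ = 74.39 or 82.09.
- r = 0.48 or 0.46; cut 23% or 21%.

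*8-week AUC for VAS, NRS, NDI, weeks 0/1/2/3/8.* Weights 0.5, 1, 1, 3, 2.5; baseline weight 0.5/8 = 6%.
- Covariance: 0.5 + 0.24 × 7.5 = 2.30.
- Variance: 17.5 + 1.8 + 39ρ = 38.8 or 46.6.
- r = 0.37 or 0.34; cut 14% or 11%.

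*8-week AUC for NPQ, EQ-5D-5L, SF-12, weeks 0/3/8.* Weights 1.5, 4, 2.5; baseline weight 1.5/8 = 19%.
- Covariance: 1.5 + 0.24 × 6.5 = 3.06.
- Variance: 24.5 + 4.68 + 20ρ = 39.18 or 43.18.
- Cut 24% or 22%. If week 3 and week 8 fall 2 and 7 weeks after baseline, the baseline weight is 14% and the cut 17 to 19%. These figures borrow 0.24 from the pain outcome.

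**In terms of power.** Where the adjusted analysis has 80% power, the t test has power Φ(2.80√(1 − r²) − 1.96). This is about 64 to 70% for the 2-week AUC and 74 to 75% for the 8-week pain AUC.

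**In terms of imbalance.** With 64 per arm the chance baseline difference has SD √(2/64) = 0.18 baseline SD. A difference of k standard errors shifts the unadjusted contrast by k × r of its own standard errors. At k = 2 and r = 0.56 the shift is 1.12. Given that imbalance, the false-positive rate is 1 − Φ((1.96 − 1.12)/√0.687), about 15%; for r = 0.37 it is about 10%.

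**Other AUC definitions (2 weeks, weeks 0/1/2).**
- Mean of the two follow-up values only: r = 0.24/√((1 + ρ)/2) = 0.28 or 0.26, cut 8% or 7%.
- Change from baseline, weights −1.5, 1, 0.5: r = −1.14/√(2.42 + ρ) = −0.67 or −0.65, cut 45% or 42%, with the imbalance entering in the opposite direction.

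**Narrower baseline spread.** If the VAS entry threshold makes the baseline SD 0.6 of the follow-up SD (assumed), the baseline weight is multiplied by 0.6. At weeks 0/1/2 and ρ = 0.5, r = (0.3 + 0.36)/√2.056 = 0.46, cut 21%. On days 0/4/11 the cut is 17%.

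**The case against.** The t test is not wrong. Under 1:1 randomisation it holds its 5% level and is unbiased on average over all allocations. A reader might infer that the AUC results will be biased or invalid; the document does not support that. The harm is lost precision, plus a shift conditional on whatever imbalance occurs.

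The AUC is also a supporting analysis. The primary outcome is the change in VAS on movement to week 3, analysed by ANCOVA, and a mixed model with group-by-time terms also covers the whole course. That stands and limits the importance of the point.

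That the AUC contains baseline is inferred, not stated. This stands as a limit on the figures, but not on the direction: the alternative definitions above still leave the AUC correlated with baseline. The 2-week figure depends on visit days, and a larger assumed baseline correlation would give larger cuts but has no source in the document, whose only value is 0.24.

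A reader might further infer that QALYs, and so the primary economic endpoint, will be compared without adjustment. The document does not say so. The t-test sentence belongs to the effectiveness analysis, and the economic text names no model for incremental QALYs. Silence there may be filled by a fuller plan.

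**Conclusion.** The point holds as an avoidable inefficiency and internal inconsistency in a stated supporting analysis. With 0.24 as the baseline correlation, a raw trapezoid AUC from baseline, equal SDs and follow-up correlations of 0.5 to 0.7, the t test forgoes a variance reduction of about 21 to 31% (2 weeks) and 11 to 14% (8-week VAS, NRS, NDI). The 2-week range reflects visit days as well as ρ. For VAS the gain falls if the entry threshold compresses the baseline SD. None of this touches the primary ANCOVA or the sample size of 128, and the QALY extension is a recommendation for consistency, not an error in the text.

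**What to change.** In section 2.11, replace the t test by a linear model of each AUC on group and the baseline value of that outcome, in line with the ANCOVA already planned. Institution, as the randomisation stratum, may be added. State how the AUC is built: raw scores or change, whether baseline is the first point, actual or nominal visit days, and which assessment closes the 2-week period for instruments not measured between baseline and week 3.

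In the economic analysis, estimate incremental QALYs from a regression on group and baseline EQ-5D-5L utility within each bootstrap replicate, so that both uses of the AUC treat baseline alike.

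The cost is a few sentences of analysis text. All baseline values are already collected; no patients, visits or data items are added.

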### Study design and setting (Fig. 1 and Table 1)

2.1

This 2-armed, parallel, multi-centered randomized controlled trial (RCT) will be conducted at four community-based hospitals in Korea; Jaseng Hospital of Korean Medicine, Daejeon Jaseng Hospital of Korean Medicine, Bucheon Jaseng Hospital of Korean Medicine, and Haeundae Jaseng Hospital of Korean Medicine. A total of 128 patients, 64 for the MSAT and 64 for the acupuncture treatment groups, will be recruited from the 4 hospitals. Treatment will be performed 2 to 3 times a week for 2 weeks, followed by a follow-up for 8 weeks after randomization (Fig. 1).

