#### Active control group: acupuncture

2.3.2

The protocol for trapezius acupuncture is as follows; Acupuncture points are selected from primary meridians (SI15, TE15, and LI16 bilateral) and extraordinary meridians (GB20, BL10, SI14 bilateral, and GV14 unilateral) on the bilateral upper and middle trapezius according to the physician's discretion. Acupuncture is performed with needles inserted into 6 to 12 selected points. Disposable needles (30 mm ∗ 0.25 mm; Dong-bang Acupuncture, Korea) are used for the insertion, and depending on the characteristics of the acupuncture point, after the perpendicular or oblique insertion, a twirling method is performed for the patient to feel the acupuncture sensation.

A total of 6 treatments will be performed 3 times a week for 2 weeks; however, depending on the patient's condition or circumstances, a total of 4 to 6 treatments may be performed when conducting the treatment twice a week. Duration for the needle insertion will be approximately 15 minutes.

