#### Relevent concomitant care

2.3.3

All treatments (drugs, surgery, nerve block, acupuncture, physical therapy, etc.) for relieve neck pain are prohibited until the 3^rd^ week (visit 9), the primary endpoint in both MSAT and control groups. There are no treatment restrictions during the f/u period after the primary endpoint. However, during the study period, acetaminophen (maximum 4 g per day) will be allowed to all subjects and the use of the drug will be recorded in a self-report method.

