##### Five-Level EuroQol 5-dimension (EQ-5D-5L)

2.4.2.8

EQ-5D indirectly estimates the quality weight of a specific health condition through a survey of the health condition through multiple aspects. It is the most widely used tool for assessing the quality of life. EQ-5D-5L is composed of 5 items (mobility, self-care, usual activities, pain, and anxiety/depression) that investigates the current health status. The subjects respond to the questions using the 5-point Likert scale. (1 = I have no problems about, 2 = I have slight problems about, 3 = I have moderate problems about, 4 = I have severe problems about, and 5 = I am unable to about) In this study, the Korean version EQ5D-5L will be used with its validity verified.^[24]^

EQ-5D-5L will be measured 3 times in total; at the baseline, week 3 (visit 8), and week 8 (visit 9).

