Considering the characteristics of non-parametric data, 95% CI of the incremental cost-effectiveness ratios of cost per QALY will be estimated using the bootstrapping technique. In addition, the probability that of MSAT being cost-effective will be examined using the cost-effectiveness acceptability curves graph according to the degree of willingness to pay. All analyses will be made for costs through the healthcare system and social perspectives.

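### The bootstrap 95% CI for the ICER has no condition attached and cannot be interpreted if replicates fall on both sides of a zero QALY difference

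*Protocol article*

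**What the plan says.** In the protocol article, Statistical analysis: "The primary economic endpoint will be the incremental cost-effectiveness ratios of cost per Quality Adjusted Life Years (QALY", comparing MSAT with acupuncture. On the horizon: "The analysis period is the entire study period including the intervention period and follow-up period", with optional extrapolation beyond it. QALYs come from EQ-5D-5L utilities by the area-under-the-curve method.

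On uncertainty, the same section says that "95% CI of the incremental cost-effectiveness ratios of cost per QALY will be estimated using the bootstrapping technique". The reason given is the non-parametric nature of the data. The next sentence adds that the probability of MSAT being cost-effective "will be examined using the cost-effectiveness acceptability curves graph according to the degree of willingness to pay". All of this is to be done from a healthcare-system and a social perspective.

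Three design features bear on how large the QALY difference could be:
- The comparator is an active treatment (section headed "Active control group: acupuncture").
- Treatment lasts two weeks, "followed by a follow-up for 8 weeks after randomization".
- In Relevent concomitant care: "There are no treatment restrictions during the f/u period after the primary endpoint".

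**The concern.** The ICER divides a cost difference by a QALY difference. Bootstrapping deals with skewed costs, which is the reason the article gives, but not with a denominator that may change sign. Two problems follow when it does:

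- **Mixed meaning.** A negative ratio arises both when MSAT is dominant (more QALYs, lower cost) and when it is dominated (fewer QALYs, higher cost). A positive ratio can likewise mean paying for a gain or saving at a loss. Ordering such values from low to high does not order them from favourable to unfavourable.
- **Divergence.** As the QALY difference approaches zero, the ratio runs off to plus or minus infinity, so the ends of the interval are set by replicates with almost no QALY difference.

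The article does not say what will be reported in that case. Cost-effectiveness is a named aim and policymakers a named audience, so the primary economic result could be published with limits that nobody can read.

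**Working it through.** **The plan's own figures.** None is given for the economic endpoint. The arm size used below comes from Sample size estimation, and that chain reproduces. A two-sample t test with effect size 0.55, two-sided 5% and 80% power needs 52.87, so 53 per group and 106 in total. The ANCOVA correction is 106 × (1 − 0.24²) = 99.9, so 100. Dropout gives 100 / 0.80 = 125, and 128 is the next total that splits evenly over four sites (32 each), or 64 per arm.

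**Inputs for the check**
- n = 64 per arm, and about 50 per arm after 20% dropout (article).
- Horizon 8/52 = 0.154 year (article).
- Sustained utility gap g = 0.01, 0.02 or 0.05 (assumed).
- SD of a patient's mean utility over the period = 0.08 to 0.12 (assumed).

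**Formulas**
- QALY difference = g × 8/52. For g = 0.02 this is 0.0031.
- SE = SD × (8/52) × √(2/n). For n = 64 this is 0.0022 (SD 0.08) to 0.0033 (SD 0.12).
- Share of replicates below zero, when the observed gap equals g: Φ(−QALY difference / SE).

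| Gap g | z (SD 0.08 / 0.12) | Replicates below zero, 64 per arm |
|---|---|---|
| 0.01 | 0.71 / 0.47 | 24% / 32% |
| 0.02 | 1.41 / 0.94 | 8% / 17% |
| 0.05 | 3.54 / 2.36 | <0.1% / 0.9% |

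With 50 per arm, √(2/50) = 0.2. A gap of 0.02 then gives z = 1.25 / 0.83, or 11% / 20%.

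The factor 8/52 cancels in z. A short horizon does not by itself push replicates across zero; what counts is the average gap relative to its SD.

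The average gap can be well below the peak gap. Utilities are taken at baseline, week 3 and week 8. If the gap is zero at baseline, 0.02 at week 3 and back to zero at week 8, the area is ½ × 3 × 0.02 + ½ × 5 × 0.02 = 0.08 utility-weeks, against 8 × 0.02 = 0.16 if sustained. That is half, so with the same SDs a 0.02 peak falls in the 0.01 row.

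**What the interval would look like.** Take an assumed QALY difference of 0.002 (SE 0.002) and an assumed cost difference of 20,000 won (SE 15,000), independent. Of the replicates, 16% have a negative QALY difference. The percentile interval runs from about −97 million to +110 million won per QALY. About 22% of the ratios are negative; roughly 65% of those are dominated and 35% dominant.

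**Coverage.** A normal-theory simulation of the percentile interval used 50 per arm, independent cost and QALY differences, and standardized cost differences of 0.2, 0.5 and 1.0.

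| Standardized QALY difference | Coverage of the nominal 95% interval |
|---|---|
| 0.05 | 86% to 92% |
| 0.1 | 94% to 96% |
| 0.2 | 96% to 98% |
| 0.3 | 98% |
| 0.55 | 97% to 98% |

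**Chance that the 95% CI of the QALY difference includes zero (50 / 64 per arm)**

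| Assumed standardized QALY difference | Chance |
|---|---|
| 0.1 | 92% / 91% |
| 0.2 | 83% / 80% |
| 0.3 | 68% / 60% |
| 0.4 | 48% / 38% |
| 0.55 | 21% / 12.5% |

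**The case against.** The strongest reply has four parts.

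1. *The likelihood is not in the article.* A reader might infer that the QALY difference will probably straddle zero here. The article gives no QALY effect, utility SD or cost. Its only effect size is 0.55. At the assumed SDs that is a utility gap of 0.044 to 0.066, and only 0.1% (64 per arm) to 0.3% (50 per arm) of replicates would be negative. This stands as a limit on the claim. However, 0.55 is the pilot effect used to size the trial, not a QALY effect, and nothing supports carrying it over in full to an 8-week QALY.

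2. *The interval is not invalid as such.* A reader might infer that it has no coverage at all. The simulation does not support that: coverage was at or above nominal from a standardized difference of 0.2 upward and clearly short only at 0.05. This stands. The main failure is of interpretation.

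3. *The type of bootstrap interval is not stated* and may be settled in a fuller plan. This stands for percentile ordering and the handling of quadrants, so their absence is not the criticism. The unconditional choice of the ratio as the quantity carrying the interval is in the article.

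4. *The acceptability curve already covers decision uncertainty.* It stays well defined when the QALY difference crosses zero, because each point is the probability that net benefit exceeds zero at that threshold. This largely stands and lowers the stakes. It does not make the interval on the named endpoint readable.

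**Conclusion.** The point holds as a minor one. The article commits without condition to a 95% CI on a ratio that becomes uninterpretable if replicates lie on both sides of a zero QALY difference, and whose coverage is unreliable when the true difference is near zero.

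How often this would happen depends on assumptions. With 64 per arm and SD 0.08 to 0.12, the share of negative replicates runs from 24–32% at a gap of 0.01 to under 1% at 0.05. The active comparator, an 8-week window of which treatment fills only two weeks, and free care in both arms after week 3 make the smaller gaps plausible. They do not establish them.

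The economic evaluation is listed among the secondary outcomes, and the primary comparison of VAS on movement is untouched.

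**What to change.** From the same bootstrap replicates and for both perspectives:

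- Report incremental cost and incremental QALY, each with a bootstrap 95% CI.
- Show the replicates on the cost-effectiveness plane.
- Report incremental net monetary benefit (willingness to pay × QALY difference − cost difference) with a bootstrap 95% CI at prespecified willingness-to-pay values, beside the planned acceptability curve.
- Keep the ICER as a point estimate, and attach an interval only if essentially all replicates lie in one quadrant.

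This changes wording only; no extra data or patients are needed. The one real cost is that the willingness-to-pay values must be named, which should be done before results are seen.
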